## Abstract

**Background:**

The global mortality caused by cardiovascular disease increases with weight. The Framingham study showed that obesity is a cardiovascular risk factor independent of other risks such as type 2 diabetes mellitus, dyslipidemia and smoking. Moreover, the main problem in the management of weight-loss is its maintenance, if it is achieved. We have designed a study to determine whether a group motivational intervention, together with current clinical practice, is more efficient than the latter alone in the treatment of overweight and obesity, for initial weight loss and essentially to achieve maintenance of the weight achieved; and, secondly, to know if this intervention is more effective for reducing cardiovascular risk factors associated with overweight and obesity.

**Methods:**

This 26-month follow up multi-centre trial, will include 1200 overweight/obese patients. Random assignment of the intervention by Basic Health Areas (BHA): two geographically separate groups have been created, one of which receives group motivational intervention (group intervention), delivered by a nurse trained by an expert phsychologist, in 32 group sessions, 1 to 12 fortnightly, and 13 to 32, monthly, on top of their standard program of diet, exercise, and the other (control group), receiving the usual follow up, with regular visits every 3 months.

**Discussion:**

By addressing currently unanswered questions regarding the maintenance in weight loss in obesity/overweight, upon the expected completion of participant follow-up in 2012, the IMOAP trial should document, for the first time, the benefits of a motivational intervention as a treatment tool of weight loss in a primary care setting.

**Trial Registration:**

ClinicalTrials.gov Identifier: NCT01006213

## Background

### Introduction

Overweight and obesity are growing health problems throughout the industrialised world. If not controlled, it then will continue to contribute to the burden of non-transmitable diseases, which is increasing constantly. There is currently clear scientific evidence of the association of obesity and a large number of diseases and their manifestations, including: diabetes, hypertension, dyslipidemia, cardiovascular events and inflammatory markers such as plasma fibrinogen levels and C-reactive protein [1,2].

Overall mortality for cardiovascular causes increases with weight [3,4] and, in the Framingham study, obesity was seen to be an independent risk factor for CVR regardless of other risk factors such as type 2 diabetes mellitus, dyslipidemia and smoking [5,6]; at the same time, overweight and obesity in adults significantly reduces life expectancy, in both women and men and smokers and non-smokers [7].

The prevalence of obesity is increasing continuously in developed countries, causing a serious public health problem. According to the SEEDO'2000 study, the figures for the prevalence of obesity in Spain (BMI>30) are 14.5% (13.3% men and 15.7% women) while the overall overweight and obesity figure (BMI>25) is 53.5% [8,9].

When treating overweight and obesity, it is considered essential that diet should be included in a general programme, together with physical exercise, lifestyle changes and psychological support. However, although significant weight loss can be relatively easily achieved in the short term, its maintenance is very difficult to get, is for this that the research that could help these patients is so important. Drug treatment of obesity should not be used as an isolated therapy, but together with other basic therapies, such as diet, physical activity and psychological support. It should be prescribed to patients with BMI>30 or >27 if associated with co-morbidities, such as diabetes mellitus, arterial hypertension, dyslipidemia, sleep apnoea syndrome [10-13].

Weight loss is a healthcare need that leads to significant savings in the estimated cost of obesity and the diseases associated to it, both directly and indirectly, which amount to more than 2,500 million euros per annum, a figure that accounts for almost 7% of total healthcare costs [14,15].

A variety of individual and group psychological therapies have been used in weight loss. In a study conducted in 20 primary healthcare centres in Great Britain, researchers evaluated the efficacy of a motivational interview to modify fat intake, physical activity and smoking in 883 patients at high risk of cardiovascular disease, obtaining a benefit in the intervention group [16].

Motivational intervention alone, in obese patients, has been shown to be effective, even in patients who only took a drug (sibutramine) for weight reduction [17]. But psychological interventions are particularly useful when combined with dietary and exercise strategies. In this review of 36 clinical studies, 26 were conducted in the United States, and only one in Spain, in diabetic obese patients [18,19].

Other studies using motivational interviews have been shown to be effective for giving up smoking [14,17], reducing alcohol intake [20,21] and improved adherence to treatment strategies in diseases as common as arterial hypertension, diabetes mellitus and bronchial asthma [22].

When making lifestyle changes in the adult population, the interventional methods are complex, because individuals tend to cling to what is familiar, even though this may be putting their health at risk [23].

All changes involve some elements that evolve and others that remain stable. The aim is to help patients make them part of their lives without affecting what they feel is essential. However, it is important to help them perceive these as necessary and beneficial so that a series of changes they make will give them an awareness that their health depends on the type of habits they change, and that these can be taken as an exercise that will improve their health and well-being[21].

However, there are no studies in our primary care environment, in cardiovascular disease, that assess the efficacy of an intervention based on a group motivation interview about weight reduction in overweight and obese patients, and the maintenance of the weight achieved over time.

Studies are required among our patients to confirm the efficacy observed in other populations and the feasibility of the group motivation intervention in overweight and obese patients, with a view to suggesting its application in the primary care setting as a tool for dealing with this health problem.

For these reasons, a study has been proposed, to compare the efficacy of the healthcare professionals' usual practices, together with a motivational group intervention vs an isolated traditional intervention on weight loss and its maintenance in overweight and obese patients (IMOAP). The purpose of this report is to present the design of IMOAP trial.

## Methods

### Study overview

This study will be randomised, multi-centre interventional, in overweight and obese patients, with a follow-up of 26 months.

The overall goal of IMOAP study is to assess whether the efficacy of the healthcare professionals' usual practices, together with a motivational group intervention (delivered by a nurse trained by an expert psychologist), is more effective than an isolated traditional intervention on weight loss and its maintenance in overweight and obese patients. Furthermore, the study will evaluate whether this result has a positive impact on quality of life, changes in eating habits, and a reduction in the associated cardiovascular risk factors and overall cardiovascular risk.

Table 1 presents the timeline of the study. Protocol development, external review occurred over an initial 4-month period beginning in 2007.

**Table 1 T1:** Timetable of the IMOAP trial

Phase	No. of Months	Calendar Dates	Trial Activities
1	4	01/07-04/07	Protocol development.
2	8	05/07-12/07	Acceptance to participate of Basic Health Areas.
3	2	01/08-02/08	Distribution and randomisation of the Basic Health Areas into both groups: Intervention/controls. For those BHA that will visit the intervention groups, training of nursing staff and coordinating the teams, creating templates and study protocols.
4	30	03/08-09/10	Main trial recruitment and follow-up
5	26	10/10-12-12	Follow-up only
6	4	12/12-04/13	Analysis and reporting

A second phase had the purpose of the acceptance to participate of Basic Health Areas.

For this, the coordinators have contacted the Basic Health Areas, to explain the protocol and confirm their participation. After this period, it has been the distribution and randomisation into the study groups: Intervention/controls. For those BHA that will visit the intervention groups, it has been done the training of nursing staff and coordinating the teams, creating templates and study protocols.

The training of the nursing staff has consisted in a basic training strategy, initially aimed at nurses and focusing on group motivation for life-style changes in overweight and obese patients, because lack of motivation is a common cause of therapeutic failure. The training has consisted of a number of workshops where role play techniques have taken place to help assimilate the concepts taught. This workshop has been delivered at the BHA of the intervention group and written material delivered regarding the content. Secondly, a written guide has been created to standardise the information the nurses provide during the overweight and obesity check-up visits. The guide includes information about the disease, healthy habits and diet.

Randomization into the study began in first trimester 2008, with a recruitment goal of 1,200 participants. The intervention and main trial recruitment will take place over 30 months with the patients in the intervention and control groups.

Finally, four months before the end of the project the final laboratory tests will be performed and the data collected for statistical analysis and reporting.

The first patient was entered on September 2008. The final visit for the last randomized participant is planned for the last trimester 2010, with final study reports expected in the first trimester of 2013.

### Selection of the study subjects

The IMOPAP inclusion and exclusion criteria are presented in Table 2. These criteria have been established to identify a trial population with overweight and obesity, and with sufficient statistical power with the proposed sample size. They will be included sequentially, from the beginning of the study. To avoid possible bias in the selection of patients, and not overburden the nursing staff, patient recruitment and follow up will be rolled out in stages during the first six months of the study to the first two patients who meet the study inclusion requirements and who present none of the exclusion criteria. This will carry out superior quality control, using smaller sample size than would be possible if we randomised the patients. The institutional review Ethics Committee of Jordi Gol i Gurina Foundation in Barcelona approved the conduct of the study. In addition, the study has been done in compliance with the Helsinki Declaration. Each IMOAP participant has provided written informed consent using procedures reviewed and approved by the EECC review board.

**Table 2 T2:** Inclusion and exclusion criteria

*Inclusion criteria*
1. Overweight (BMI>25) and obese (BMI>30) patients of both genders, registered in the medical history (MH) or recently diagnosed.
2. Aged between 30 and 70 years
3. Agreement to participate in the study

*Exclusion criteria*
1. Patients with severe clinical pathology (bedridden, dementia, advanced neoplasia, etc.)
2. Patients with secondary obesity (hypothyroidism, Cushing's disease, etc)
3. Patients with severe sensorial disorders capable of interfering with the motivational intervention (severe, uncorrected deafness, severe visual deficit, etc).
4. Patients with serious psychiatric disorders

### Measurements

A wide range of interview, physical examination, and laboratory data are being collected (Table 3), with the frequency of measurement varying by group assignment, but at least at baseline, at one year and at the end of the trial. The weight measurement will be done always in the same conditions (the patient wearing underwear only, barefoot, and at the same time of day). Body Mass Index (BMI) will be calculated as: Weight in kilos divided by height in square metres W (kg)/H (m2). Waist measurement will be defined as the midline between the edge of the lowest rib and the iliac crest alongside the anterosuperior iliac spine, in cm. The cardiovascular risk factors will also be assessed: Hypertension will be defined as either blood pressure readings of above 140/90 on three occasions, (in diabetics, above 130/80); or patients receiving treatment for hypertension or with a clinical diagnosis of hypertension; Diabetes Mellitus: By case history or two prandial glycaemia readings > 126 mg/dl; -Smoking: packets year.

**Table 3 T3:** Measures

1. Questionnaires
a. Sociodemographics: age, ethnicity, sex.
b. Detailed initial medical history; abbreviated interval history focused on eligibility criteria, CVD, smoking status and diabetes mellitus. Inter-current processes: diseases, level of care they have received, start and end of the process.
c. Concomitant medications:
d. Quality of life and food assessment through SF questionnaire 36 validated in Spain by Alonso [24]
e. Dietary survey, 3 day record, (quantitative and qualitative) at the beginning and end of the study [25].
f. Questionnaire drafted specifically for this study, described in table 4.
2. Physical examination measures
a. Anthropometric measurements: standing height in centimetres (cm), weight in kg, waist circumference
b. BP and pulse
3. Laboratory measures
a. Fasting serum glucose
b. Fasting lipid panel (Total Cholesterol, HDL-Cholesterol, LDL- Cholesterol)

Quality of life and food assessment through SF questionnaire 36 validated in Spain by Alonso [24], and dietary survey, 3 day record, (quantitative and qualitative) at the beginning and end of the study [25].

A questionnaire, drafted specifically for this study, and administered by the participating nurse, gathers the variables mentioned.

### Outcomes

The primary endpoint for the IMOAP is to assess whether the efficacy of the healthcare professionals' usual practices, together with a motivational group intervention (delivered by a nurse trained by an expert psychologist), is more effective than an isolated traditional intervention on weight loss and its maintenance in overweight and obese patients.

This will be calculated as the percentage of patients reducing their weight by 5% and maintenance over time. The strategies for facing change and working in the groups [26-28] consist in providing information and practical advice on modifying eating habits, starting or increasing regular physical activity, lifestyle changes, functioning of the metabolism, management of the obesity and its complications, smoking as a cardiovascular risk factor, food diary, shopping methods and, finally, the number of calories to ingest.

### Formation of the patient groups

Groups will be made up according to the following criteria: mixed, women and men, aged between 30 and 70 years, and a maximum 15 and minimum 7 members per group. Each nurse could manage 3 different groups (1 per month). The random assignment of the intervention will be done at the primary care Basic Health Areas (BHA), in L'Hospitalet de Llobregat, neighbouring areas and Barcelona city. Two groups will be formed in separate centres, one of which will receive the motivational group intervention (intervention group) and the other the standard treatment (control group). To prevent possible bias, the BHA located in the same building will be assigned to the same group (control or intervention). The participating healthcare professional (nurse) will select the first two patients with visits during the pre-established recruitment period, who met the study criteria.

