### Sample size calculation

The number of subjects necessary to divide into two independent groups has been calculated. With the standard intervention, a weight reduction of 5% of weight is expected (P1) [30,31]. It was predicted that the experimental intervention would lead to 75% of the patients reducing their weight by 5%. It will be assumed an alpha risk of 0.05 (bilateral hypothesis) and a beta risk of 0.20 (a potential 80%). If the interventions will be assigned individually, in other words, per patient, the number of patients in each group would be 328 (756 in total). If we assume a percentage loss of 20% and apply a correction according to the formula Na = N [1/1-R)] where N is the theoretical number of subjects, Na is the corrected number of subjects and R is the expected proportion of loss, a total of 946 patients would be necessary. Given that the assignment of the interventions will be done by BHA, we had to increase the sample size because of the design effect [28]; if 24 BHA (clusters) were to participate, 12 per type of information, it would be K = [m(1-CCI)]/[Z-(CCI × m)] where K = number of subjects per cluster, m = 473 patients per intervention, Z = number of clusters per type of intervention = 12 and ICC = intra-class correlation coefficient. We assumed that the basic ICC for the percentage of obese patients who would reduce their weight by 5% was 0.005. The number of patients in each BHA (Cluster) would be 50. 50 subjects × 12 BHA = 600 patients per arm or type of intervention. 600 subjects × 2 interventions = a total of 1,200 patients.

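### The 80% power behind 1,200 patients makes no allowance for correlation within therapy groups, which exist in the intervention arm only

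*Protocol article*

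**What the plan says.** **Delivery (protocol article, Formation of the patient groups; Motivational intervention in the intervention group).** Intervention patients meet in groups with "a maximum 15 and minimum 7 members per group" for 32 one-hour sessions over 26 months. A nurse may run up to three groups.

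**Control arm (Intervention control group).** Patients are seen every three months; no group sessions are described.

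**Sample size (Sample size calculation).** The authors state that "we had to increase the sample size because of the design effect" and give assignment by BHA as the reason. They assume that the ICC for the proportion of obese patients who "would reduce their weight by 5% was 0.005". This one value is used with 473 patients and 12 clusters in each arm, and gives 50 patients per BHA, 600 per arm and 1,200 in total. The target is 80% power at two-sided 5%, with 75% of intervention patients expected to reach the 5% weight loss and 20% lost.

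**Analysis (Statistical analysis).** The comparison uses multilevel techniques on individual patient values. The levels are not named.

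**The concern.** Patients who share up to 32 sessions, and are meant to share experience and reinforce one another (Table 5), can be expected to have correlated outcomes within their therapy group. That correlation adds to any correlation within the BHA and has no counterpart in the control arm. A single ICC applied equally to both arms cannot represent a component found in only one of them.

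What is at stake is power. Any positive therapy-group correlation inflates the variance of the intervention proportion, so the trial may have less than its stated 80% chance of detecting the planned difference. If group membership is not recorded, the correlation also cannot be estimated afterwards, and a null result would be harder to interpret.

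**Working it through.** **1. Reproduce the plan's figure.** With m = 473, Z = 12 and ICC = 0.005:

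K = 473 × 0.995 / (12 − 0.005 × 473) = 470.635 / 9.635 = 48.8, so 49 per BHA, 588 per arm and 1,176 in total.

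This agrees with the stated 50, 600 and 1,200 apart from rounding. The BHA-level ICC alone accounts for the figure, so no group-level term is in it.

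**2. Number of therapy groups.** 600 intervention patients in groups of 7 to 15 make about 600/15 = 40 to 600/7 = 86 groups, or roughly 3 to 7 per BHA.

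**3. Control rate (assumption).** The article does not give it as a proportion of patients: "With the standard intervention, a weight reduction of 5% of weight is expected (P1". It has to be back-solved, and the starting number is itself inconsistent, since "the number of patients in each group would be 328 (756 in total" does not double correctly (2 × 328 = 656; 756/2 = 378). Against 75%, with 80% power and two-sided 5%:
- 328 per arm corresponds to a control rate of 65.0%;
- 378 per arm, the figure carried forward (756/0.8 = 945, stated as 946, half of which is 473), corresponds to 65.7%.

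Both readings are shown.

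**4. Add the therapy-group term.** After 20% loss there are n = 480 per arm, k = 40 per BHA and, for groups of 12, g = 9.6.

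- Control design effect: 1 + 39 × 0.005 = 1.195
- Intervention design effect: 1.195 + (g − 1) × ICC_group
- SE² = p1(1 − p1) × 1.195/480 + 0.75 × 0.25 × DE_int/480
- Power = Φ[(0.75 − p1)/SE − 1.96]

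Example, p1 = 0.657 and ICC_group = 0.05: DE_int = 1.195 + 8.6 × 0.05 = 1.625; SE = √(0.000561 + 0.000635) = 0.03458; 0.093/0.03458 = 2.689; power = Φ(0.729) = 76.7%.

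| Group ICC (assumed) | DE_int | Power, control 65.7% | Power, control 65% |
|---|---|---|---|
| 0 (BHA only) | 1.195 | 82.7% | 87.5% |
| 0.01 | 1.281 | 81.4% | 86.5% |
| 0.02 | 1.367 | 80.2% | 85.4% |
| 0.05 | 1.625 | 76.7% | 82.3% |
| 0.10 | 2.055 | 71.2% | 77.1% |

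For groups of 12, power falls below 80% only above a group ICC of about 0.02 (65.7%) or 0.07 (65%). For groups of 7 the thresholds are about 0.04 and 0.13.

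**5. Sensitivity to the formula and group size.** With a pooled-variance formula, the BHA-only power is 82.3% (65.7%) and 87.3% (65%). Over group sizes 7 to 15 and group ICC 0.01 to 0.10, it then runs from 81.6% down to 65.8%, and from 86.7% down to 72.1%.

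**6. Type I error.** The null case was simulated with 12 BHAs per arm, 40 patients analysed in each, therapy groups of 10 and a BHA random effect only (6,000 runs). Rejection rates were 5.1 to 6.2% with a normal reference and 3.8 to 5.0% with a t reference on 22 df. The effect of the omission is on power.

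**The case against.** **The size is unknown.** The documents give no group ICC, and at 0.01 to 0.02 the loss for groups of 12 is only about 1 to 3 points, with power still at or above 80%. This stands. A reader might infer that the trial is underpowered; the documents do not support that, because the result depends on two quantities they do not state, the group ICC and the control rate.

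**The total of 1,200 has slack.** This stands in part. A reader might infer that any margin above 80% comes only from the 328/756 conflict and vanishes once 378 per arm is used. It does not: the 65.7% reading still has about 83% with BHA clustering only. At that rate 378 × 1.195 = 452 completers per arm are needed and 480 are expected, because loss is added before clustering and the cluster size is rounded up to 50. But this margin was not planned for therapy groups, and on the 65.7% reading a group ICC of about 0.02 uses it up.

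**The ICC of 0.005 may already include the groups.** The text does not say so. Even if it did, for groups of 15 it would cover a group ICC of at most 0.005 × 49/14 = 0.0175, with nothing left for the BHA.

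**Model structure belongs in the analysis plan.** This stands. The multilevel wording does not exclude a therapy-group level, and nothing in it commits the trial to equal between-cluster variance in the two arms. A reader might infer such an assumption from the single planning ICC, but a planning value is not a model specification. The sample size, however, is fixed in the article, and a later choice of model cannot restore power that was not planned for.

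**Sharing a nurse is not peculiar to the intervention arm.** This also stands: participating nurses select patients without restriction to one arm. The point rests on the shared group sessions only.

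**Conclusion.** The concern holds as an unaccounted source of variance. The design effect covers BHA clustering alone, while the group sessions create a further level of clustering in the intervention arm only. The direction is certain for any positive group ICC. The size is not, because the documents do not give that ICC.

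The figures rest on groups of 12, 20% loss falling evenly, a BHA ICC of 0.005, a normal reference and a back-solved control rate. Over an assumed group ICC of 0.02 to 0.10, the loss from the BHA-only power is about 2 to 11 points. Power ends between about 80% and 71% if the control rate is 65.7%, and between about 85% and 77% if it is 65%. The planned analysis is not shown to be invalid. The point is minor in severity, but it bears on a figure the trial relies on.

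**What to change.** 1. Restate the power for 1,200 patients with both levels of clustering, over a stated range of therapy-group ICCs and group sizes. Give the control rate as a proportion of patients and settle the 328/756 conflict in the same passage, since the restated power depends on both.
2. Record a therapy-group identifier for each intervention patient while the trial is running; membership is hard to reconstruct later.
3. In the analysis plan, let the multilevel primary model include therapy group as a random effect nested in BHA, in the intervention arm only (a partially nested model).

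The cost is one extra variable, a few sentences of text and probably a slightly lower stated power. No extra patients are needed.
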